### Outcome measurements

A background information questionnaire is included, comprising sociodemographic variables such as sex, age, educational level, size of community, place of birth, number of siblings, birth order, living situation, other health conditions and medication (obtained from self-report and medical file).

Standardised questionnaires are used to assess primary and secondary outcomes. Table 1 presents an overview of the characteristics and psychometric properties of the questionnaires used.

**Table 1 BMJOPEN2016014593TB1:** Psychometric properties of the questionnaires used in STEPSTONES-ConHD

Variable	Subject	Measurements	Items	Validity	Reliability	Responsiveness	Interpretation
Primary outcome							
Patient empowerment	AD	GYPES	15	Construct validity supported an adequate model fit of a five factor solution (df: 80; χ^2^: 154–948, p<0.0001; CFI: 0.916; RMSEA: 0.068; SRMR: 0.069) (data on file) Face validity confirmed in young persons with chronic conditions (data on file)	Internal consistency confirmed in young persons with CHD, α=0.819 (data on file)	Floor scores: 0%; ceiling scores: 1.5% (data on file)	Score from 15 to 75. Higher score reflects a higher level of patient empowerment
Secondary outcomes							
Transition readiness	AD	RTQ adolescent version	26	Validity based on relationships with other variables confirmed in young persons with kidney transplant,^27^ p.91–92	Internal consistency confirmed in young persons with kidney transplant; α values over 0.70^27^	NR	Scores from 10 to 40. Higher scores denote increased adolescent or caregiver responsibility.
	PA	RTQ parent version		Construct validity reported for parents of young persons with kidney transplant,^27^ p.91–92	Reliability reported for parents of young persons with kidney transplant; α values over 0.70,^27^ p.90	NR	
Knowledge on ConHD	AD	KnoCoMH	19	Validity was confirmed in adults with CHD in relation to discrimination ability, the relationship of the items and the construct of interest,^28^ p.232–234 KnoCoMH is based on the Leuven Knowledge Scale which has been validated in young persons with CHD,^29^ p.79–80	Internal consistency and test–retest reliability confirmed,^28^ p.232–234	NR	Scores are calculated by dichotomising the answers (correct/incorrect) for each domain
Health behaviours	AD	HBS-CHD	15*	Item content validity, scale content validity index and validity based on relationships to other variables confirmed in adolescents with CHD,^30^ p.548	Stability not confirmed^29^	Confirmed in adolescents with CHD by Guyatt's Responsiveness Index,^30^ p.551	Substance use, dental hygiene and total health risk score from 0 to 100. Physical exercise score from 0 to ∞
Patient-reported health	AD	PedsQL generic module	23	Convergent validity, measurement invariance and factor structure confirmed in paediatric populations, 31 p.336–337 32 p.1507–1510	Test–retest reliability and internal consistency show α values over 0.70 in paediatric populations,^32^ p.1507 31 p.333–335	Minimal clinically important difference reported for young people with CHD was 6.0 for the total score.^33^	Scores from 0 to 100. Higher scores indicate a better perceived health status.
		PedsQL cardiac module	27	Convergent validity was confirmed,^34^ p.215	Internal consistency for majority of scales exceeded α values of 0.70,^34^ p.214	Minimal clinically important differences reported for young people with CHD ranged from 7.6 for symptoms to 12.6 for communication.^33^	Scores from 0 to 100. Higher scores indicate lower problems.
		EQ-5D-3L	5	Convergent and discriminative validity confirmed in patients with cardiovascular disease,^35^ p.6	Test–retest reliability confirmed in cardiovascular patients,^35^ p.6	Confirmed in patients with cardiovascular disease,^35^ p.6	Scores from 1 (no problems) to 3 (extreme problems) on five dimensions Scores from 0 (worst imaginable health state) to 100 (best imaginable health state)
Quality of life	AD	LAS	1	Validity based on relationship with Satisfaction with Life Scale found to be highly correlated (ρ=0.52). Test content confirmed in adults with CHD (100% of patients understood the wording and format)^36^ Validity has been evaluated in adolescents with CHD.^37^ ^38^	Test–retest reliability confirmed in adults with CHD (ICC=0.65),^36^	Confirmed in adults with CHD (floor scores=0%, ceiling scores=2.7%)^36^	Score is from 100 (best imaginable health status) to 0 (worst imaginable health status).
Healthcare usage	AD	Healthcare usage questionnaire	11	NA	NA	NA	NA
Parental uncertainty towards transfer to adult care	PA	LAS	1	Face validity confirmed in parents of young persons with chronic conditions (data on file). Test content confirmed in parents of young persons with CHD (100% of patients understood the wording and format).	NR	Floor scores: 7.8%; ceiling scores: 4.8% (data on file)	Score is from 0 (very uncertain about the transfer to adult care) to 100 (not uncertain about the transfer of care).

AD, adolescents; CFI, comparative fit index; CHD, congenital heart disease; EQ-5D-3L, EuroQoL 5 dimensions 3 levels; GYPES, Gothenburg Young Persons Empowerment Scale; HBS-CHD, Health Behavior Scale-Congenital Heart Disease; ICC, intra-class correlation; KnoCoMH, Knowledge Scale for Adults with Congenitally Malformed Hearts; LAS, linear analogue scale; NA, not applicable; NR, not reported; PA, parents; PedsQL, Pediatric Quality of Life Inventory 4.0; RMSEA, root mean square error of approximation; RTQ, Readiness for Transition Questionnaire; SRMR, standardised root mean square residual; STEPSTONES, Swedish Transition Effects Project Supporting Teenagers with chrONic mEdical conditionS.

#### Primary outcome measures

The primary outcome is patient empowerment, defined as “an enabling process or outcome arising from communication with the healthcare professional and a mutual sharing of resources over information relating to illness, which enhances the patient's feelings of control, self-efficacy, coping abilities and ability to achieve change over their condition”.^9^ Empowerment includes five dimensions: (1) identity; (2) knowledge and understanding; (3) personal control; (4) decision making; and (5) enabling others.^9^

Since no questionnaire to measure the level of empowerment in young persons with chronic conditions exists, we developed the Gothenburg Young Persons Empowerment Scale-Congenital Heart Disease module (GYPES-CHD). The scale has 15 items, 3 items for each of the aforementioned dimensions. Each item is answered on a five-point Likert scale: strongly disagree; disagree; neither agree nor disagree; agree and strongly agree. A total score is calculated by summing the item scores. The total score ranges from 15 to 75 points, with a higher score reflecting a higher level of patient empowerment.

Face validity was confirmed after cognitive interviews with six young persons with CHD. The psychometric properties of this scale were examined in a cross-sectional study in 205 young persons with CHD. Internal consistency of the items was confirmed with a Cronbach's α of 0.821. No floor or ceiling effect in scoring was observed. A complete description of the psychometric evaluation of GYPES will be provided in another article.

#### Secondary outcomes measures

We will measure six secondary outcomes in the adolescents: transition readiness, health behaviours, knowledge about CHD, healthcare usage, quality of life and patient-reported health. In the parents, we will measure transition readiness (proxy) and parental uncertainty towards transition.

#### Transition readiness

Transition readiness is defined as the “adolescent's readiness to assume complete responsibility for their healthcare and their readiness to transfer to adult medical care”.^27^ Transition readiness is evaluated using the Readiness for Transition Questionnaire (RTQ), adolescent and parent versions. These questionnaires examine two aspects. First, the overall transition readiness is assessed, using two items ranging from 1 to 4. The sum of these two items results in a score ranging from 2 to 8. Second, the frequency of adolescent responsibility and parental involvement are reported in 10 different health behaviours, on a five-point Likert scale. Each variable results in a total score ranging from 10 to 40, and higher scores indicate higher adolescent responsibility or parental involvement, respectively.

#### Knowledge about CHD

Adolescents' knowledge about their CHD is assessed with the Knowledge Scale for adults with Congenital Malformed Hearts (KnoCoMH).^28^ This instrument evaluates the level of knowledge within four domains: disease and its treatment; complications prevention; physical activity; and reproductive issues.^28^ The questionnaire includes 19 items and scores are calculated by dichotomising answers as correct or incorrect. Access to the medical files is needed in order to confirm the answers in some of the items. For participants for whom medical treatment or endocarditis prophylaxis is not recommended, the domains are excluded.

#### Health behaviours

Health behaviours are measured with the Health Behavior Scale-CHD. Health behaviours are ‘activities a person undertakes to maintain or improve health and prevent diseases’.^30^ This scale assesses alcohol consumption, tobacco use, dental care and physical activity. The scale has 15 items that help to calculate three summary risk scores: substance use (score 0–100), dental hygiene (score 0–100) and total health risk score (score 0–100). Higher risk scores represent unhealthier behaviours.

#### Patient-reported health

Patient-reported health is assessed by the generic and cardiac modules of the Pediatric Quality of Life inventory 4.0 (PedsQL 4.0), as well as the EuroQoL 5 dimensions 3 levels (EQ-5D-3L). The PedsQL 4.0 provides information on health status in relation to psychosocial and physical health.^32^ The generic module consists of 23 items that cover four dimensions: physical; emotional; social functioning and school functioning. Items are answered by using a five-point Likert scale: never, almost never, sometimes, often and always. For each dimension, a scale score can be calculated, which ranges from 0 to 100. Further, a physical health summary score, a psychosocial health summary score and a total score can be calculated.

The cardiac module contains 27 items that cover six dimensions: symptoms; treatment; perceived physical appearance; treatment anxiety; cognitive problems and communication. Each item is answered using a five-point Likert scale (never, almost never, sometimes, often and always). As in the generic version, scores are transformed on a scale from 0 to 100, and then a mean subscale core is calculated.^34^

The EQ-5D-3L comprises a descriptive system and a visual analogue scale (VAS). The descriptive system has five dimensions (mobility, self-care, usual activities, pain/discomfort and anxiety/depression) with three response categories per dimension.^39^ The participants are asked to indicate which statement is most suitable in relation to their health status. The VAS measures the participants' self-rated health on a scale with the end points ‘best imaginable health possible’ (=100) and ‘worst imaginable health state’ (=0). The descriptive system allows for the determination of a five-digit health state that combines the level of perceived problems in each dimension (level 1: indicating no problem, level 2: indicating some problems and level 3: indicating extreme problems). Information obtained from the descriptive system can be converted to a single summary index by assigning values to each level of every dimension.

#### Quality of life

Quality of life is defined as “the overall degree of life satisfaction that is positively or negatively influenced by individuals’ perception of certain aspects of life important to them, including matters both related and unrelated to health”.^40^ This variable is measured using a 10 cm linear analogue scale (LAS),^36^ where the participants indicate in the scale how they judge their current quality of life. The scale looks similar to the VAS of the EQ-5D, but has the end points ‘best imaginable quality of life’ (=100) and ‘worst imaginable quality of life’ (=0).

#### Healthcare usage

Healthcare usage within the preceding 6 months is measured in relation to their CHD and other possible conditions. The measurement consists of six dimensions: hospital stay; healthcare contact; specialised care; emergency care; school absence and follow-up unit after transfer to adult care. This assessment was developed to be used in the APPROACH-IS project.^41^ After the transfer to adult care, we will assess the proportion of patients who are in follow-up in a GUCH unit, both in the intervention and control arms.

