#### Usual care (intervention, control and comparison group)

All adolescents who participate in the study receive usual care, irrespective of whether in the intervention, comparison or control group. Usual care includes visits to an outpatient paediatric cardiology clinic where they meet a nurse and a paediatric cardiologist. Disease complexity determines the frequency of the visits. None of the participating centres have a TC as a part of usual care and there is no documentation of transition plans. It is common practice in Sweden that patients are transferred to adult care around the age of 18 years.

Since usual care can vary across clinics and over time, an assessment of transition-related practices will be carried out in all the centres at the beginning of the intervention and at the end of the study. This assessment will comprise three elements: (1) a structured survey called CHAT (Congenital Heart Adolescent and Transition; on file); (2) interviews with healthcare professionals who are involved in the care for adolescents with CHD in the participating centres and (3) observations of the routine during the clinic visits.

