### Follow-up period and data collection

During the 2-year follow-up period, outcome measurements are assessed on three different occasions: T0, baseline when the participants are 16 years old; T1, midterm when the participants are 17 years; and T2, final data collection when the participants have been transferred to adult care and are ∼18.5–19 years old (see figure 1).

Participants from the intervention group will be mailed the set of questionnaires 1 month before the outpatient clinic visit. If the questionnaires have not been received by the time of the visit, they will have the opportunity to complete them while waiting for their appointment. Patients from the control and comparison groups may not have a scheduled outpatient visit. Therefore, data collection in these groups is completely undertaken by post when the participants are 16 (T0), 17 (T1) and 18.5 years old (T2).

To minimise non-response in the comparison and control groups, a modified Dillman procedure will be used.^26^ Two weeks after the documents are sent, non-responders will receive a first personalised reminder in the form of a text message. If after 4 weeks the questionnaires have not been received, a reminder letter and a new set of questionnaires is sent. After 6 weeks, persistent non-responders are contacted by telephone and asked whether they received the questionnaires, if the mailing address is correct, if they want a new set of questionnaires and if they want to continue participating in the study. After 8 weeks, a last reminder is sent to those who agree to participate in the study during the telephone call.

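### The 6-month healthcare-usage look-back ends just before a clinic visit in the intervention arm but at a fixed age in the comparison arm, so scheduled contacts are counted under different rules in two randomised arms.

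*Protocol article*

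**What the plan says.** Healthcare usage is one of six secondary outcomes in the adolescents (protocol article, *Secondary outcomes measures*). The *Healthcare usage* section sets one look-back for all arms: "Healthcare usage within the preceding 6 months is measured in relation to their CHD and other possible conditions". It lists the content: "The measurement consists of six dimensions: hospital stay; healthcare contact; specialised care; emergency care; school absence and follow-up unit after transfer to adult care". A scheduled cardiology visit would most naturally be recorded under healthcare contact or specialised care.

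The section *Follow-up period and data collection* sets the timing of the forms by arm. For the intervention arm: "Participants from the intervention group will be mailed the set of questionnaires 1 month before the outpatient clinic visit". Those who have not returned the forms by then are covered too: "they will have the opportunity to complete them while waiting for their appointment". For the other two groups the article explains that "Patients from the control and comparison groups may not have a scheduled outpatient visit", and so "data collection in these groups is completely undertaken by post when the participants are 16 (T0), 17 (T1) and 18.5 years old (T2").

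On how often patients are seen, the *Usual care* section says only: "Disease complexity determines the frequency of the visits". No interval is given. T2 is described as "final data collection when the participants have been transferred to adult care and are ∼18.5–19 years old".

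**The concern.** A look-back count depends on where its window sits in the patient's visit cycle. In the intervention arm the window closes zero to one month before a visit, which is the end of a cycle if that visit is the routine one. In the comparison arm it closes at an arbitrary point. The timing rule is assigned together with the arm, so randomisation does not balance it, and nothing in the article aligns the two windows.

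If routine visits are well spaced, the intervention arm would report fewer scheduled contacts than the comparison arm even with identical care. At T1 that could be read as an effect of the programme. At T0 it would look like a baseline imbalance. The *Statistical analyses plan* section adjusts the complementary analysis of covariance for baseline variables that differ significantly, so baseline usage, if it is among the variables screened, could enter the model only because of form timing.

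**Working it through.** **The plan's own figure.** The article states no figure for healthcare usage. The randomised arm size used below is its 63 per arm. With a difference of 5.25 and an SD of 5.25/0.5 = 10.5, n = 2 × (1.96 + 0.84)² × (10.5/5.25)² ≈ 63, and 63/0.90 = 70 after dropout. Both reproduce.

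**Inputs from the article.** Look-back of 6 months. Intervention form completed u months before the index visit (the visit that triggers the mailing), with u between 0 and 1. Comparison form at a fixed age.

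**Assumptions, because the article is silent.** Routine visits every V months, with the same V in both arms. The index visit is the routine visit. Comparison-arm visit dates are unrelated to the mailing age.

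**Intervention arm.** The index visit lies after the form, so it is outside the window. The previous visit was V − u months before the form. It is inside only if V − u ≤ 6, that is V ≤ 6 + u, so V is at most 7 months.

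**Comparison arm.** Time since the last visit is uniform on 0 to V. The expected number of visits in the window is 6/V, and the chance of at least one is min(1, 6/V).

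| V (months) | Intervention, visits in window | Comparison, expected visits in window |
|---|---|---|
| 3 | 2 | 2 |
| 4 | 1 | 1.5 |
| 5 | 1 | 1.2 |
| 6 | 1 | 1 |
| 6.5 | 0 if completed in the waiting room, 1 if completed a month ahead | 0.92 |
| 7 | 0 if completed in the waiting room, 1 if completed a month ahead | 0.86 |
| 12 | 0 | 0.50 |
| 18 | 0 | 0.33 |
| 24 | 0 | 0.25 |
| 36 | 0 | 0.17 |

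Above 7 months the gap always has the same sign. At 7 months or less it can shrink, vanish or, at 6.5 to 7 months with early completion, reverse.

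**What this could do to a test.** As an illustration, take any scheduled visit in the window as a binary variable, with 63 per arm and a two-sided 5% test. This endpoint is mine, not the protocol's. The chance of a significant result with no true difference is Φ[(d − 1.96·s₀)/s₁], where d is the difference in proportions, s₀ its pooled and s₁ its unpooled standard error.

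- One third of patients each at 6, 12 and 24 months: intervention (1 + 0 + 0)/3 = 33.3%; comparison (1 + 0.50 + 0.25)/3 = 58.3%. With s₀ = 0.0888 and s₁ = 0.0859, (0.25 − 0.174)/0.0859 = 0.88, giving about 81%.
- Half at 6 and half at 12 months: 50% versus 75%, giving 83%.
- Half at 6 and half at 24 months: 50% versus 62.5%, giving 29%.
- First mix, but only half of index visits are the routine one: intervention 0.5 × 33.3% + 0.5 × 58.3% = 45.8%, against 58.3%, giving 29%.
- No index visit is the routine one: no difference in routine visits, and the nominal 5%.

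**After alignment.** With the same age-defined window in both arms, equal visit rates give equal expected counts, for example 0.50 versus 0.50 for annual visits.

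**The case against.** The strongest objection concerns which visit triggers the intervention mailing. The article does not say that it is the next routine cardiology visit. The *Intervention* section defines the programme by visits with the transition coordinator, and the remark that the other groups may have no scheduled visit suggests that intervention patients may have one because of the programme. If those visits are scheduled independently of routine care, routine visits fall at an unrelated phase in both arms and their expected counts are equal. This stands, and the conclusion has to be conditional on it.

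Three further limits also stand. No visit interval is given, so no single figure is an estimate. Hospital stay, emergency care, school absence and the proportion in GUCH follow-up, which is the one comparison the *Healthcare usage* section names, are not affected in this way. At T2 the article does not say which visit precedes the post-transfer form, and the third coordinator visit or an earlier adult-clinic visit could fall inside the window.

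It may also be said that the usage questionnaire and the analysis plan are not shown, and that how contacts are counted belongs there. That is fair for the counting rules. It does not answer the point, because the two timing rules and the look-back are all stated in the article, and visits outside the window are not captured by the form for a later analysis to recover.

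**Conclusion.** The concern holds in a limited form. Two randomised arms have scheduled contacts ascertained under different stated rules, and the index visit is always outside the intervention arm's window. Where that visit is the routine one and intervals exceed about 7 months, the intervention arm's count under healthcare contact and specialised care is too low at T0 and T1 with no difference in care. Under the assumed intervals the chance of a visit in the window is 0% versus 50% at 12 months, 0% versus 25% at 24 months and 0% versus 17% at 36 months.

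A reader might infer more: that scheduled visits as a whole drop out of the intervention arm, that a false finding of reduced usage is likely at the final assessment, or that the false-positive risk is about 81%. The documents support none of these. Only the index visit is excluded by rule, the sign at T2 cannot be determined, and the 81% belongs to one assumed mix and falls to 29% or to the nominal 5% under others equally compatible with the text.

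The outcome is secondary, and the primary outcome and its sample size are untouched. The mechanism follows from stated rules and the repair is cheap, so the change is worth making.

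**What to change.** Use one reference period in all arms, in either of two ways:

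- print the same age-defined 6-month dates on every usage form, with the end date no later than the earliest completion in any arm; or
- mail the usage form at the same ages in every arm, apart from the visit-linked set.

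In addition, report scheduled CHD outpatient visits and programme visits separately from unscheduled care, so that contacts created by the programme are not mixed with other use.

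Two apparent alternatives are not adequate substitutes. Asking about the time since the last questionnaire keeps windows that differ by arm, because completion dates differ by arm. A medical-file count would not capture school absence or care received elsewhere.

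The cost is a change of wording or one separate mailing in the intervention arm, and slightly less recent recall for some participants. No extra patients or visits are needed.
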